**Fig. 1 Fig1:**
[figure not shown]
MyComrade study design

A total of 16 practices will be recruited (eight in ROI; eight in NI), and four practices in each jurisdiction will be randomly allocated to the intervention or control arms. Patients with multimorbidity who are prescribed 10 or more repeat prescription medications will be identified in each practice. From each practice, 20 patients with multimorbidity will be recruited, providing a total of 320 participants. The list of 20 consented patients from each practice will be shared with participating GPs/PBPs. In the intervention arm, pairs of GPs/GP and PBPs will use the MyComrade intervention and will be asked to complete collaborative medication reviews before the 4-month follow-up time point. ROI pairs will be GP-GP, and NI pairs will be GP-PBP. Control practices will proceed with usual care. Participant data will be collected from primary care practice records and postal questionnaires sent to participants at baseline before randomisation takes place and at 4 and 8 months after the date of randomisation. Qualitative interviews to assess the study feasibility and acceptability and to explore experiences related to multimorbidity management will be conducted with a purposive sample of GPs and PBPs participating in the study, practice administration staff and patients.

A Public and Patient Involvement group has been established, involving four adults (two women and two men) from both NI and ROI and living with multimorbidity. This group have provided input into the patient recruitment materials, and qualitative interview guides, and will provide input into the interpretation of the qualitative findings and methods for disseminating the study findings. The establishment and running of this group as research partners in this study are guided by the PPI Ignite @ NUI Galway programme office, part of a national PPI programme funded by the Health Research Board in Ireland.

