### Recruitment

Primary care practices will be contacted by the research team via several communication pathways: the Northern Ireland Clinical Research Network (NICRN) Primary Care network, the HRB Primary Care Clinical Trials Network of Ireland (HRB PC CTNI), ROI and NI business directories, local GP education events and meetings and local GP social media groups. Practices will be sent information on the study and asked to express an interest in taking part. Interested practices will be contacted by a member of the research team to further discuss the study. Before recruitment, each practice will be provided with instructions and asked to run a search in their record system to assess the number of potential participants based on their number of prescription medications (target > 60 potentially eligible patients per practice). Practices will be informed at the outset of the material supports associated with participation in the study and details of the implementation of the intervention (Table 1).

Eligible patients will be identified in NI and ROI using electronic record search procedures. These search procedures will be modified to take into account the different electronic practice record systems used in both jurisdictions. In the ROI, a search procedure developed and tested in another Irish primary care multimorbidity trial [32] will be used to identify eligible patients. In NI, a similar search procedure will be developed by the study team and pilot tested for the two main electronic practice record systems there. To comply with the General Data Protection Regulation (GDPR), only practice staff members will review the list of eligible patients generated by the search procedure and apply the study eligibility criteria. Eligible patients will receive a recruitment pack, consisting of an invitation to participate in the study, a participant information leaflet, and a consent form. Recruitment packs will be provided by the study team but will be addressed and posted by the practice teams, to adhere to GDPR. To minimise selection bias, patients will be randomly selected from the list of eligible patients, and recruitment packs will be sent out until 20 patients from each practice consent to participate.

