#### Progression criteria

The progression criteria for this study (Table 2) were developed based on Avery et al.’s Top Ten Tips for guiding the decision to progress from a pilot to a definitive trial, focusing on key acceptability and feasibility variables [37]. Several rounds of discussions were held within the study team to draft the criteria outlined in Table 2. Discussions were guided by existing literature, study team experience, the pilot study design and potential barriers and facilitators to practice and patient involvement. As part of the process evaluation within this study, qualitative and quantitative data will be collected for the investigation of the following outcomes: feasibility of practice recruitment, feasibility of patient recruitment, feasibility of practice retention, feasibility of patient retention and feasibility of intervention implementation.

**Table 2 Tab2:** MyComrade progression criteria

	Go—proceed with RCT	Amend—proceed with changes	Stop—do not proceed unless changes are possible
**1. Feasibility of practice recruitment** Can 16 practices be recruited to take part in 3 months (8 practices in NI and 8 in ROI)?	If > 14 practices are recruited to take part in 3 months	If > 14 practices are recruited, but it takes longer than predicted (e.g. 3–6 months)	Unable to recruit practices
**2. Feasibility of patient recruitment** Can 20 patients per practice (total *N* = 320) be recruited?	If 20 patients are recruited in one month per practice; a total of 320 (100%)	If 10–19 patients are recruited in one month per practice; a total of 160–319 (50 to < 100%)	If < 10 patients are recruited in one month per practice; a total of < 159 (50%)
**3. Feasibility of practice retention** Can > 14 practices be retained in the study until completion?	> 14 (88%) retained	> 12 (75%) retained	< 12 retained
**4. Feasibility of patient retention** Can at least 80% of recruited patients be retained in the study until completion?	> 256 (80%) retained	224–255 (70–80%) retained	< 224 retained
**5. Intervention implementation**	Delivery of intervention judged strongly feasible by qualitative data	Delivery of intervention judged feasible by qualitative data	Delivery of intervention judged possibly feasible by qualitative data

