### Sample size

As this is a pilot study, a formal sample size calculation was not done [38]. This study aims to recruit 16 primary care practices (eight in NI and eight in ROI) and 20 patients per practice (*N* = 320), based on recommendations from Eldridge et al. [20] and the CONSORT guidance [21] on the minimum number of clusters required in pilot and definitive cRCTs, respectively. The aims of this pilot cRCT are to investigate feasibility and acceptability and to identify the most suitable primary outcome(s) for a definitive cluster randomised trial. The estimates from this pilot trial will be used to calculate the sample size needed using the methods outlined by Rutterford et al. [39].

Based on an assessment of the number of practices and practice sizes in the region, we will invite 50 patients per practice and, a priori, have defined a success criterion as 40% of the total number of participants invited to be recruited to the research evaluation (approximately 20 patients per practice).

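### Table 2 row 2 states each patient-recruitment tier both per practice and as a fixed total for 16 practices, with no governing rule, and the two can give different adjacent verdicts

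*Protocol article*

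**What the plan says.** Protocol article, Outcomes, Progression criteria, Table 2 row 2. The row asks: "Can 20 patients per practice (total *N* = 320) be recruited". Its three cells each join a per-practice count to an overall total with a semicolon:

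- Go: "If 20 patients are recruited in one month per practice; a total of 320 (100" per cent.
- Amend: "If 10–19 patients are recruited in one month per practice; a total of 160–319 (50 to < 100" per cent.
- Stop: "If < 10 patients are recruited in one month per practice; a total of < 159 (50" per cent.

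The totals presuppose the full set of practices (Trial design, under Fig. 1): "A total of 16 practices will be recruited (eight in ROI; eight in NI". Row 1 of the same table, however, gives Go for any number of practices above 14 recruited in three months, so 15 is enough.

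Two other sections bear on the count. Recruitment says that "recruitment packs will be sent out until 20 patients from each practice consent to participate". Sample size says that "we will invite 50 patients per practice" and sets "a success criterion as 40% of the total number of participants invited to be recruited to the research evaluation (approximately 20 patients per practice".

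**The concern.** Patient recruitment is one of the primary outcomes, and row 2 is the pre-specified rule for judging it. Each cell presents two conditions as if they were one. They are the same condition only if there are exactly 16 practices and the per-practice figure is a mean. The article states neither. It does not say whether both conditions must hold, which prevails, or whether the per-practice count applies to the average practice, to every practice or to any practice.

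If the conditions can disagree, the tier reported depends on a choice that the plan has not made. Recruitment had already finished when the article was submitted (Study status), so that choice cannot now be assumed to be blind to the counts.

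**Working it through.** **Inputs, all from the article.** Practices: 16 planned; 15 still gives Go on row 1. Target: 20 per practice, at which mailing stops. Row 2 tiers: 20 / 10–19 / under 10 per practice; 320 / 160–319 / under 159 in total.

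**The plan's own figures.** 16 × 20 = 320 and 16 × 10 = 160 = 50% of 320. So the total limits are the per-practice limits times 16. The Stop limit is the exception, printed as under 159 (159/320 = 49.7%), so a total of exactly 159 has no tier. The Sample size criterion gives the same target: 0.40 × 50 × 16 = 320.

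**Reading A: the count applies to each practice and the lowest practice decides (16 practices).**

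| Pattern | Total | By total | Lowest practice |
|---|---|---|---|
| 10×18 + 6×8 | 228 | Amend | Stop |
| 15×20 + 1×9 | 309 | Amend | Stop |
| 8×19 + 8×10 | 232 | Amend | Amend |
| 8×9 + 8×3 | 96 | Stop | Stop |

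If every practice has at least 10, the total is at least 160, so the reverse clash cannot arise. The Amend/Stop conflict needs at least one practice under 10 and a total from 160 to 15×20 + 9 = 309. If instead a tier must literally hold in all practices, some results fit no per-practice tier at all, for example 8×20 + 8×10 = 240.

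**Reading B: the count is a mean (10–19 taken as 10 to below 20).**

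- 16 practices: mean = total/16, so 160 gives 10 and 320 gives 20. The two parts agree at every total except 159 (mean 9.94, Stop; no tier by total).
- 15 practices: 15 × 20 = 300 is Go per practice but Amend by total. 15 × 10 = 150 is Amend per practice but Stop by total. With mailing stopped at 20, the total cannot exceed 300, so Go by total is out of reach although every practice met its target.

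**How often reading A would bite: illustration only.** Assumptions not in the article: consent varies between practices as a beta-binomial with correlation ρ; the lowest practice decides; 16 practices, each capped at 20. Share of simulated trials with total Amend and at least one practice under 10, with 50 invitations per practice:

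| Mean consent | ρ = 0 | ρ = 0.05 | ρ = 0.10 |
|---|---|---|---|
| 30% | 48% | 97% | 99% |
| 35% | 10% | 81% | 96% |
| 40% (the plan's figure) | 1% | 52% | 84% |

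With 60 invitations, the entry for 40% consent and ρ = 0.05 falls from 52% to 27%.

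**The case against.** The best defence is that per practice simply means on average. The totals are the per-practice limits times 16, and Sample size sets success as a share of all those invited and then restates it as about 20 per practice. On that reading, with 16 practices, the conflict disappears apart from the 159 gap. This stands, and it is a reasonable guess at the intention. But the article never says mean, and the reading fails once 15 practices are recruited, a number that row 1 accepts.

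A second objection is that the simulated frequencies prove little. They let a single practice decide the tier, the correlation is assumed, and they stop at 50 invitations although Recruitment describes mailing until 20 consent. This also stands. The range is 1% to 99%. Under the same model with 50 invitations, cases where at least half the practices are under 10 while the total is 160 or more make up only 0%, 0.5% and 3.9% of trials at 30% consent (ρ = 0, 0.05, 0.10), and about 0% at 40%.

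A reader might infer that any uneven recruitment gives opposite verdicts. The article does not support that. 8×19 + 8×10 is uneven and Amend on both counts. The clashes are between neighbouring tiers, never Go against Stop, and the Stop column itself leaves room to proceed if changes are possible.

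Finally, the criteria guide the decision alongside qualitative evidence, and cluster size is to be examined in any case. That limits the harm of an unclear tier but does not tell the reader which tier applies.

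**Conclusion.** The point holds in a limited form. Row 2 carries two definitions with no rule for combining them, and they can return different adjacent tiers in two situations:

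- the count is applied to each practice with the lowest deciding, at least one practice is under 10, and the total is 160 or more;
- 15 practices are recruited, even if the count is a mean.

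The second needs no distributional assumption and follows from rows 1 and 2 alone. The first depends on a reading that the article neither states nor excludes. No single frequency of conflict can be claimed. The defect is in the wording of a stated decision threshold for a primary outcome; it is worth correcting and does not undermine the pilot.

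**What to change.** Score row 2 on one definition: the total recruited within the one-month window, as a percentage of 20 × the number of practices recruited. Go is 100%, Amend is 50% to below 100%, Stop is below 50%. Drop the fixed per-practice and total counts as separate tests.

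The denominator must follow the number of practices, because a fixed 320 makes Go unreachable with 15. Under this rule 300/300 = 100% is Go, 150/300 = 50% is Amend, 228/320 = 71% is Amend, and 159/320 = 49.7% is Stop, which also closes the gap at 159.

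Report the number of practices under 10 beside the verdict, as description for planning cluster size and not as a second test. Since recruitment was complete at submission, label the choice as a clarification, and where the per-practice and total readings differ, report the verdict under both.

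The cost is one reworded table row and a sentence in the report. It uses only recruitment counts by practice, which the existing per-practice criterion already requires.

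### The Table 2 progression cut-offs in rows 2 to 4 contradict their own percentages or leave boundary results without a verdict, and row 1 gives Stop no number

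*Protocol article*

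**What the plan says.** The Progression criteria section of the protocol article has a table (Table 2) that sorts each primary feasibility outcome into Go, Amend or Stop. The denominators are 16 practices and 320 patients: "Can 16 practices be recruited to take part in 3 months (8 practices in NI and 8 in ROI" and, in Trial design, "providing a total of 320 participants".

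- **Row 1, practice recruitment.** Go is "If > 14 practices are recruited to take part in 3 months". Amend needs the same number over a longer period, with 3–6 months as an example. Stop is "Unable to recruit practices", with no number.
- **Row 2, patient recruitment.** Go is 320, Amend is 160–319, and Stop is "a total of < 159 (50"%).
- **Row 3, practice retention.** Go is "> 14 (88%) retained", Amend is "> 12 (75%) retained", and Stop is fewer than 12. The row's question also uses the strict sign with 14.
- **Row 4, patient retention.** The question is whether 80% or more of recruited patients can be kept. Go is "> 256 (80%) retained", Amend is 224–255 (70–80%), and Stop is fewer than 224.

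The Study status section reports that practice and patient recruitment had finished at submission and that data collection would end in March 2021.

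**The concern.** A progression rule should give each possible result exactly one verdict, and its count and percentage should describe the same bar. Here the signs and percentages disagree in rows 3 and 4, some totals fall between columns, and row 4 uses counts where its question concerns a proportion of recruited patients.

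These rows judge four of the five primary outcomes. The Discussion relies on the criteria being specified in advance. If a result lands on an affected value, someone must decide after seeing it whether the sign or the percentage governs, and the benefit of specifying the rule in advance is lost for that row.

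**Working it through.** **Inputs.** 16 practices, 320 patients and the Table 2 cut-offs listed above.

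**Step 1: reproduce the printed percentages.** Taken as bare integers, the cut-offs match their labels: 14/16 = 87.5% (prints as 88%), 12/16 = 75%, 256/320 = 80% and 224/320 = 70%. For row 2, 159/320 = 49.7%, which gives 50% only by rounding. The fault therefore lies mainly in the strict signs.

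**Step 2: apply the signs as written.**

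| Cell | Smallest or largest count that qualifies | Actual percentage | Printed percentage |
|---|---|---|---|
| Row 3 Go, more than 14 | 15 | 15/16 = 93.75% | 88% |
| Row 3 Amend, more than 12 | 13 | 13/16 = 81.25% | 75% |
| Row 4 Go, more than 256 | 257 | 257/320 = 80.3% | 80% |
| Row 2 Stop, fewer than 159 | 158 | 158/320 = 49.4% | 50% |

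Of the counts 0–16, only 14 rounds to 88% and only 12 equals 75%. The signs exclude both from the cells that carry those labels.

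**Step 3: run every total through the literal rules.**

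- Row 2 (0–320): 159 has no verdict.
- Row 3 (0–16): 12 has no verdict. 15 and 16 meet both Go and Amend, because Amend has no upper limit. 14 is Amend only, but it carries the 88% printed under Go.
- Row 4 (0–320): 256 has no verdict, although it is exactly 80% and meets the row's question.
- Row 1 (0–16): 15 and 16 are Go or Amend according to time. For 1–14 there are two readings. If Stop means that no practice could be recruited, these counts have no verdict. If it means failing to exceed 14, all are Stop, so 14 practices recruited on time is Stop while 15 is Go, with no Amend band for number.

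**Step 4: test row 4 when fewer than 320 are recruited.** Row 2 allows 160–319 as Amend. The number retained cannot exceed the number recruited, so:

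- 160–223 recruited: at most 223 retained, which is below 224. Row 4 is Stop even at 100% retention.
- 224–255 recruited: Amend at best, even at 100% retention.
- 300 recruited (illustration): 0.80 × 300 = 240 retained meets the 80% question, but 240 lies in the Amend range.

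**Step 5: check the repair.** With row 2 Stop below 160; row 3 Go 14 or more, Amend 12–13, Stop below 12; and row 4 Go 256 or more, Amend 224–255, Stop below 224 (for 320 recruited), every total in rows 2 to 4 receives exactly one verdict.

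**The case against.** The strongest reply is that this is loose labelling in a feasibility pilot. The strict sign with 14 appears in both row 1 cells, in the row 3 question and in row 3 Go, so it may well be intended, with the bracketed percentages at fault. The criteria inform a decision and do not bind it, and even the Stop column allows progress if changes can be made. The gaps at 159 and 256 are each one patient wide.

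Much of this stands and limits the point. Several stronger readings that a reader might infer are not supported:

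- **That 14 retained has no verdict.** It is Amend by count. The conflict is only with the percentage under Go.
- **That more than 14 practices recruited after six months fits no column.** The 3–6 month range is marked as an example of slow recruitment, so a later finish can be read as Amend.
- **That 1–14 practices recruited is certainly unclassified.** This depends on reading the Stop cell as meaning none.
- **That 12 or 14 retained practices are the likeliest results.** The article gives no retention forecast.
- **That the progression decision could be chosen at will.** The ambiguity is confined to the values listed, and the row verdicts only inform the decision.

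The reply does not remove the contradiction. If the strict signs are meant, the 88% and 75% are wrong and 12 still has no verdict. In row 4, the question itself supports including 256. Nor is this detail left to another document: the article prints the thresholds, and nothing elsewhere in it resolves them.

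**Conclusion.** The point holds for rows 2 to 4 as written. In row 3 the effective bars are 94% and 81% where 88% and 75% are printed, 12 retained has no verdict, and 15–16 satisfy two columns. The overlap is minor, since most readers would take Go first. Single-value gaps remain at 256 retained and 159 recruited patients. The row 4 counts match 80% and 70% only if exactly 320 patients are recruited, and they force Stop for 160–223 recruited whatever the retention.

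For row 1 the supported conclusion is narrower: Stop has no number, so a shortfall to 1–14 practices is either unclassified or all Stop.

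The row 3 percentages assume 16 practices as denominator. The documents do not settle whether the sign or the percentage in row 3 carries the intent. Rows 3 and 1 and the row 4 denominator carry most of the weight. The thresholds should be corrected because they judge primary outcomes and the correction costs little.

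**What to change.** - **Row 2:** Stop < 160.
- **Row 3:** choose one version. If the percentages are intended: Go ≥ 14 (88%), Amend 12–13 (75% to < 88%), Stop < 12. If the strict signs are intended: Go ≥ 15 (94%), Amend 13–14 (81–88%), Stop ≤ 12.
- **Row 4:** Go ≥ 80%, Amend 70% to < 80%, Stop < 70% of patients actually recruited, noting that these equal 256 and 224 only if 320 are recruited.
- **Row 1:** state which existing verdict applies to 14 or fewer practices. This review proposes no new bands, because recruitment is complete and any new number would be set with the result known.

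Date the correction. Say openly that the row 1 and row 2 clarifications came after recruitment ended, and state whether the row 3 and row 4 changes were made before or after retention was known. The cost is the wording of one table and a short statement; design, sample and data collection do not change.

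### Table 2 row 4 asks about 80% of recruited patients but is scored on fixed counts that hold only if all 320 are recruited

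*Protocol article*

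**What the plan says.** The Progression criteria section (under Outcomes) sets out Go, Amend and Stop in Table 2.

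- **Row 4, patient retention.** The question is "Can at least 80% of recruited patients be retained in the study until completion". Go is "> 256 (80%) retained", Amend is "224–255 (70–80%) retained" and Stop is "< 224 retained". The Stop cell gives a count with no percentage.
- **Row 2, patient recruitment.** Go needs all 320. The Amend cell covers "a total of 160–319 (50 to < 100"%), so the table expects that the study may continue with far fewer than 320.
- **Row 3, practice retention.** The question is "Can > 14 practices be retained in the study until completion". Go is "> 14 (88%) retained" and Amend is "> 12 (75%) retained"; Stop is fewer than 12. Both question and score are counts.

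The Sample size section gives the target of 16 practices with 20 patients each, 320 in all. The article states no rule for adapting the row 4 counts to the number recruited. The Outcomes section lists patient retention among the primary outcomes.

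**The concern.** A retention criterion should measure what happens to patients after they join. Row 4 says it does, but its cut-offs give the intended percentages only when exactly 320 patients join. With fewer, the row partly measures recruitment, which row 2 has already scored. A recruitment shortfall could then be reported as a retention failure, and the team would look for a remedy in the wrong place when designing the definitive trial. The Discussion says that findings against these criteria will strongly indicate whether a full-scale trial is appropriate, so the scoring needs to be unambiguous before retention is known.

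**Working it through.** **Inputs.** Planned total 16 × 20 = 320 (Sample size). Row 4 cut-offs: Go above 256 (at least 257), Amend 224–255, Stop below 224 (Table 2). Recruitment accepted as Amend: 160–319 (Table 2, row 2).

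**Reproducing the plan's figures.** 0.80 × 320 = 256 and 0.70 × 320 = 224. Both match, so the counts are the percentages worked out at the target.

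**Retention needed when R patients are recruited.** Go needs 257/R; Amend needs 224/R. The fourth column takes the smallest whole number that is at least 0.80 × R and scores it by the counts. The last column scores R itself, meaning no dropout.

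| R | Go needs | Amend needs | Retained at 80%, and score | Score at 100% retention |
|---|---|---|---|---|
| 320 | 80.3% | 70.0% | 256: no category | Go |
| 300 | 85.7% | 74.7% | 240: Amend | Go |
| 280 | 91.8% | 80.0% | 224: Amend | Go |
| 272 | 94.5% | 82.4% | 218: Stop | Go |
| 257 | 100.0% | 87.2% | 206: Stop | Go |
| 256 | impossible | 87.5% | 205: Stop | no category |
| 240 | impossible | 93.3% | 192: Stop | Amend |
| 224 | impossible | 100.0% | 180: Stop | Amend |
| 223 | impossible | impossible | 179: Stop | Stop |
| 160 | impossible | impossible | 128: Stop | Stop |

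**Reading the table.**

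- R = 160–223: Stop at any level of retention, although row 2 rates this recruitment as Amend.
- R = 224–256: Go is out of reach. Full retention gives Amend at 224–255 and no category at 256.
- R = 257–319: Go is possible but needs more than 80%, rising from 257/319 = 80.6% to 257/257 = 100%.
- R = 320: exactly 256 retained is 80% and satisfies the question. It is not above 256, and the Amend band ends at 255, so it has no category.

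**Row 3.** 14/16 = 87.5% (printed as 88%) and 12/16 = 75%, so the printed percentages assume 16 practices. More than 14 means at least 15, and 15/16 = 93.8%, not 88%. Exactly 12 practices is neither above 12 nor below 12, so it has no category. With 15 recruited, the only shortfall that row 1 accepts, full retention still scores Go. With 15 recruited and one lost, 14/15 = 93.3% exceeds the printed 88% but scores Amend.

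**The case against.** The strongest reply is that the counts are only the percentages worked out at the target, and that a sensible reader would apply the percentages because the question names recruited patients. The arithmetic at 320 is indeed correct. But the Stop cell prints only a count. If 200 are recruited and all 200 stay, retention is 100%, which meets the Go percentage, while 200 is below 224, which meets the Stop count. The article does not say which governs.

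A second reply is that little hangs on one row. Stop is itself qualified by whether changes are possible, the Abstract describes the criteria as guiding the decision, and there is no stated rule for combining rows. Any total below 320 already misses Go on row 2, so at 300 or 280 recruited the usual effect is a second Amend. This stands, and it limits the consequence: the documents do not support saying that the table mechanically produces a wrong decision. The serious effect is the false Stop.

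Three stronger readings are tempting and do not hold:

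- A reader might infer that any shortfall forces Amend or Stop on retention. It does not: Go is ruled out only at 256 or fewer recruited.
- A reader might infer that row 3 has the same fault. It asks for a count and scores a count, so question and score agree. Recruiting 14 or fewer practices already misses both Go and Amend on row 1.
- A reader might want retention tied to return of the final questionnaire. The article also collects follow-up data from practice records, so a patient could remain in the study without returning it. Nothing here supports imposing that definition.

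Finally, the Study status section says recruitment was complete at submission, so any change comes after the number recruited was known. That is a fair caution about how the change is reported. It is not a reason to leave the row ambiguous.

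**Conclusion.** The point holds for row 4. The question is a proportion of recruited patients, and the score is a count fixed at 80% and 70% of 320. Across the 160–319 range that row 2 accepts as Amend, the counts are stricter than the stated percentages. They give an unavoidable Stop at 160–223, no possible Go at 224–256, and a raised Go threshold at 257–319. A shortfall can also turn retention of exactly 80% into Stop, as with 192 of 240. Separately, exactly 256 retained is unclassified.

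This rests on applying the cells as printed and on the absence of any rescaling rule in the article. It needs no assumption about actual dropout. Because row 4 is a pre-specified threshold for a primary outcome and the correction is inexpensive, it should be corrected. Row 3 needs only a lesser clarification.

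**What to change.** **Row 4.** Score retention as patients retained divided by patients actually recruited: Go at 80% or more, Amend from 70% to below 80%, Stop below 70%. Show at least 256, 224–255 and below 224 only as the worked example for 320. The example must start at 256, not above it, to agree with the rule and to close the gap. At other totals the same rule gives, for instance, Go from 240 and Amend 210–239 when 300 are recruited, or Go from 192 and Amend 168–191 when 240 are recruited.

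**Row 3.** State whether the count or the printed percentage governs, since above 14 means 93.8% and not 88%, and assign exactly 12 practices to a category.

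**Cost.** The change is to the wording of Table 2, with no new data and no change to conduct. Because recruitment was already complete, it should be dated, described as a clarification of the pre-specified criteria, and reported in the results paper. The sponsor should judge whether it needs handling under the amendment process described in the Data management and protection section.
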